**Fig 2 pone.0309935.g002:**
[figure not shown]
Randomization flow chart and protocol for intervention measurements.

## 3. Randomization and blinding

By doing so, we aim to eliminate or reduce potential biases due to the order of patients and any transference effects that might occur if one profile clinical patient will influence the performance in several evaluations. All individuals in the treatment cohort will be overseen by two physiotherapists with extensive experience (>10 years). One physiotherapist will administer the interventions for all two groups, while the other will perform the evaluations, ensuring that the second physiotherapist remains blinded to the evaluated group. An unbiased outcome ascertainment will be ensured by an independent researcher who will create a table of random numbers using an Excel formula to blind data collectors and outcome adjudicators. A block randomization design with block sizes of 4 or 8 will be applied to ensure equal distribution of participants across each group. The randomization sequence will be secured on a USB drive and stored under lock and key by an independent researcher, accessible only when necessary. A single-blind design will be employed due to the impossibility of blinded participants and the treating physiotherapist for exercise intervention. Specifically, each patient will complete a sequence of allocation in the order of A, B, B, A, where ’A’ represents SCS treatment isolated, and ’B’ denotes combined treatment. Subsequently, the average of the two ’A’ conditions was calculated, and the same process was applied for the ’B’ conditions.

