**Fig 1 pone.0309935.g001:**
[figure not shown]
Execution schedule–recruitment, intervention, and reassessment.

This study will be a research protocol for two groups: SCS and core and control motor exercises with an allocation ratio of 1:1. Data will be collected from April 2024 to January 2026. All participants will sign an informed consent form, prepared in accordance with the ethical guidelines of the Helsinki Declaration [29]. The study protocol was approved by the Ethics Committee on January 24, 2024 (ID: 2023 10 1435). This study was prospectively registered in the Clinical Trials (Registration number: NCT06272539) (Supplementary file 1)

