### 2.3 Study population

The participants will be patients diagnosed with spinal pain syndrome who are undergoing SCS at the Pain Unit at the Hospital of Salamanca. The participants will be selected according to the compliance criteria established by the criteria established by the guidance Neurostimulation Appropriateness Consensus Committee (NACC) of neurostimulation practice [36]. All patients will be informed of all the study procedures, and those of interest will be provided with a brief introduction to the selection process.

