## 4. Sample size

The sample size will be estimated using GPower® software (Franz Faul, Universität Kiel, Kiel, Germany), version 3.1.9.2. As there are no similar studies allowing for the calculation of sample size based on reference means and standard deviations, a comparison will be made using the difference between two dependent means of 1.95 normal populations, assuming equal standard deviations of 3,2 according to the results obtained from a prior study [37]. Thus, the calculation will be based on the primary outcome of "Disability" and will consider an effect size of 0.70, a power of 0.95 for ANOVA repeated measures, and an alpha error of 0.05. A total of 40 participants (20 subjects per group) will be included in this study. Moreover, considering the probability of loss during follow-up (30%), 12 more participants considering dropout (6 participants per group) will be included, resulting in a total of 52 participants. The possibility of increasing the number of subjects will be explored in case of insufficient statistical power to reach these predefined levels. In the event of dropouts, noncompliance, or absence of results, an intention-to-treat analysis will be conducted.

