## 7. Oversight and monitoring

The investigator members ([name] and [name]) who concurred on the study design and applied for funding will comprise the trial steering committee. The principal responsibility of both principal investigators will be to coordinate the execution of the study within the Pain Unit. The remaining participants will actively contribute to the coordination of the patients, application of the treatments, and management of any adverse effects that may arise. In the event of any serious adverse event occurring during the study, the principal investigators will notify the research ethics committee of the “Comité de Ética de la Investigación con medicamentos del Área de Salud de Salamanca” (IBSAL) to take the necessary measures. Furthermore, patients will be contacted by telephone during and after the trial to monitor for any adverse effects.

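### Section 3 publishes the only block sizes (4 or 8) of a single-centre trial with open assignments, so anyone who enrols and knows past assignments could be certain of some upcoming ones

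*Protocol article*

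**What the plan says.** Section 3 (Randomization and blinding) of the protocol article fixes the scheme: "A block randomization design with block sizes of 4 or 8 will be applied to ensure equal distribution of participants across each group". No other size is mentioned. Section 2.1 gives two groups "with an allocation ratio of 1:1", and section 4 plans for recruitment "resulting in a total of 52 participants".

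The trial has one centre. Section 2.3 recruits patients "who are undergoing SCS at the Pain Unit at the Hospital of Salamanca", and section 7 says: "The principal responsibility of both principal investigators will be to coordinate the execution of the study within the Pain Unit".

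Assignments are open to some people once made. Section 3 says: "A single-blind design will be employed due to the impossibility of blinded participants and the treating physiotherapist for exercise intervention". It also has a single physiotherapist deliver the interventions in both groups, while a second one evaluates blind to group. The abstract calls the trial double-blind, but section 3 is explicit that participants and the treating physiotherapist are not blinded.

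Two safeguards are stated. An independent researcher creates the list and keeps it locked away on a USB drive (section 3), and randomisation follows consent and the eligibility check (section 2.2).

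**The concern.** Locking the list away protects the file. It does not stop someone inferring the next assignment from those already made. In a blocked 1:1 scheme the arms must balance at each block end, so the history carries information. When the complete set of block sizes is public, that information sometimes becomes certainty.

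If the next arm can be anticipated at enrolment, a patient can be approached sooner, later or not at all. Some exclusion criteria in section 2.4, such as those for severe pathologies and for neurologic or psychiatric problems, leave room for judgement. The primary outcome (Oswestry disability index, section 5.1.1) is self-assessed, and the experimental arm depends on attendance and home exercise. Placing more motivated patients in that arm would favour it. Adjusting for the baseline outcome (section 8.2.2) would not correct a difference in unmeasured motivation, and a blinded evaluator does not protect against selection before randomisation.

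**Working it through.** The protocol gives no predictability figure, so there is none to reproduce.

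**Inputs.** Block sizes 4 or 8 (section 3); 1:1 allocation (section 2.1); 52 patients (section 4). How often each size is used is not stated. Shares of size-4 blocks of 25%, 50% and 75% are assumed.

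**How publication creates certainty.** Suppose the first three assignments are A, A, A. A block of 4 holds only two As, so the block must be of size 8, with one A and four Bs left. The next is B with probability 4/5. After A, A, A, A the next four must all be B. A reader who did not know the sizes would also guess B, but could not be sure.

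**Guesser who knows the sizes are 4 or 8.** For each possible position (block size b, with a As among the n assignments so far in the block) the guesser holds a weight w, and P(next = A) = Σ w·(b/2 − a)/(b − n) / Σ w. The weights are updated by the probability of each observed assignment. When a block may have ended, weight passes to a new block of either size. The guesser picks the likelier arm. Simulated over sequences of 52:

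| Share of size-4 blocks (assumed) | Correct | Certain | At least 75% confident |
|---|---|---|---|
| 25% | 66.8% | 9.4% | 33% |
| 50% | 67.7% | 7.4% | 40% |
| 75% | 69.0% | 4.2% | 37% |

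A repeat run at 50% gave 67.9% correct, 7.1% certain and about 40% high-confidence. For 52 patients, that is 0.07 × 52 ≈ 4 certain assignments and 0.40 × 52 ≈ 21 high-confidence ones.

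**Guesser who knows no sizes.** Always guessing the arm that is behind gives 67.7% correct in the 50:50 mix, the same average hit rate.

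**Single fixed size, for comparison.** For a block of 2m, expected correct guesses are m + 2^(2m−1)/C(2m,m) − 1/2, and expected certain assignments with known boundaries are 2m/(m + 1).
- Size 4 (m = 2): (2 + 8/6 − 0.5)/4 = 70.8% correct; (4/3)/4 = 33% certain.
- Size 8 (m = 4): (4 + 128/70 − 0.5)/8 = 66.6% correct; (8/5)/8 = 20% certain.

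**After the change.** Sizes 4, 6, 8 and 10 at equal probability (an assumption), with the guesser conservatively allowed to know them: 66.6% correct, 1.3% certain, about 28% at least 75% confident. For 52 patients, that is 0.013 × 52 ≈ 1 certain and 0.28 × 52 ≈ 15 high-confidence.

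**The case against.** Two block sizes with an independently held list are a conventional choice, and publication is not what produces the two-in-three hit rate: a guesser who knows no sizes does equally well on average. That stands. Small blocks with open assignments drive the average; publication adds certainty and high confidence.

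It is also fair that section 3 names only participants and the treating physiotherapist as unblinded. Section 7 says the principal investigators coordinate execution. It does not say that they enrol patients or see a running list of assignments, and no section says that the treating physiotherapist recruits. A reader might infer that the enrolling staff see every assignment, but the article does not say so. An article may leave who enrols to the full protocol, so that silence is not a fault in itself.

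Consent and eligibility already precede randomisation in section 2.2, so asking for release after eligibility would largely repeat the plan. That order does not help, however, if the next arm is anticipated before the patient is approached.

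Finally, there may be little left to change. Section 2.1 has data collection from April 2024 to January 2026, at most 22 months, and section 2.5 has an 18-month visit. If both hold, enrolment lasts about 22 − 18 = 4 months at most and may already be over.

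**Conclusion.** The point holds in a limited form. The published sizes, the single centre and the open assignments together let anyone who enrols and knows the history be certain of about 7% of assignments (4% to 9% across the assumed mixes) and at least 75% confident about roughly 40% (33% to 40%). This rests on 4 and 8 being mixed at random with the size of each block hidden, and on 52 patients.

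Three stronger readings are not supported:
- That publishing the sizes causes the 68% hit rate. It does not; the rate is the same without that knowledge.
- That a third or a fifth of assignments are certain. Those figures need one fixed size and known block boundaries, whereas the text gives two sizes.
- That enrolment has been steered, or that the Excel-made list recalculates and so is not pre-set. Nothing in the article says either; section 3 describes a list that is created and then secured.

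What remains is an avoidable route to selection bias that is cheap to narrow.

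**What to change.** Remove the block sizes from section 3. State instead that they vary at random and are recorded in a restricted document withheld from everyone who enrols or treats. Have the independent researcher generate any assignments not yet made with randomly varying sizes that include undisclosed, preferably larger ones. Because 4 and 8 are already public, deleting the numbers alone does nothing for a scheme that continues to use only those two.

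The gain is in certain and high-confidence predictions; the average hit rate hardly moves, so the change should not be described as making allocation unpredictable.

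The cost is a short amendment and a slightly larger possible imbalance if recruitment stops mid-block: at most half the largest block, so 5 patients with blocks up to 10 against 4 with blocks up to 8.

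If enrolment is complete, the sequence cannot be changed. The trial report should then say who enrolled patients and whether they knew past assignments.

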### 2.2 Informed consent

After assessing the patient and obtaining pertinent information, individuals who willingly express their interest in participating in the study and have signed the necessary informed consent forms will be chosen based on predetermined eligibility criteria. These selected participants will then be randomly assigned.

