### 2.5 Procedure

Once the groups have been established, there will be six sample collections: Pre, Post3weeks, Post2months, Post6months, Post12months and Post18months (Fig 2). Patients will be introduced to the CORE neuromuscular and control motor exercise protocol after surgery.

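### Section 3 describes a fixed A-B-B-A sequence completed and averaged within each patient, which contradicts the parallel-group blocked randomisation that the rest of the protocol describes

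*Protocol article*

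**What the plan says.** Section 3 (Randomization and blinding) begins with an ordinary parallel-group scheme. An independent researcher makes a random-number table in Excel, and the sequence is kept locked away. On blocking it says: "A block randomization design with block sizes of 4 or 8 will be applied to ensure equal distribution of participants across each group". Participants and the treating physiotherapist are not blinded.

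The section then says that "each patient will complete a sequence of allocation in the order of A, B, B, A". It defines A as SCS alone and B as the combined treatment, so the letters are the two trial arms. It continues: "Subsequently, the average of the two ’A’ conditions was calculated", and does the same for B.

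On timing, Section 2.2 describes patient assessment and consent, followed by: "These selected participants will then be randomly assigned". Section 2.5 says: "Once the groups have been established, there will be six sample collections: Pre, Post3weeks, Post2months, Post6months, Post12months and Post18months".

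**The concern.** Section 3 holds two incompatible accounts of how patients receive treatment. In one, each patient is randomised to one arm and compared with patients in the other. In the other, every patient passes through both treatments twice in the same order, and the contrast is made within the patient.

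Random, concealed allocation is what allows a difference between the arms to be read as an effect of adding exercise. A-B-B-A is the only allocation order the article spells out, and the averaging sentence is an instruction for handling data. Someone following them literally would have nothing to randomise. Someone reading them as the list order would have a sequence that is not random. In neither case would the trial be the one that Section 8.2.2 analyses.

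**Working it through.** The article gives no figure on this point to reproduce. The main check is to set its sections side by side; a short calculation then covers the alternative reading.

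**Step 1. Literal reading: each patient goes through A, B, B, A.** This needs four treatment periods per patient, a measurement at the end of each, and an analysis that handles period and carry-over. The article has instead:

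- Section 2.1: two groups with 1:1 allocation.
- Section 2.5: one Pre and five follow-up measurements up to 18 months, with no change of treatment between them. There are no two A and two B results per patient to average.
- Section 4: 20 patients per group, raised to 26 per group (52 in total) for dropout. Under the literal reading there would be no groups.
- Section 4.1: patients are randomised to receive an intervention. The exercise programme in Section 4.1.1 is a single progressive course that continues beyond day 90, with no washout and no second course.
- Section 8.2.2: between-group differences at each time point from mixed models with a group-by-time interaction, and no period, sequence or carry-over term.

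The literal reading therefore contradicts five other sections and the first half of Section 3.

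**Step 2. Alternative reading: A, B, B, A is the order for four successive patients.**

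- Balanced orders in a block of 4: 4!/(2! × 2!) = 6. A-B-B-A is one of them.
- Balanced orders in a block of 8: 8!/(4! × 4!) = 70.
- If the same block were repeated, one order would be possible and 100% of assignments would be known in advance.

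For comparison, take properly permuted blocks of 4 and a guesser who knows the block size and all past assignments:

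- Assignments that can be deduced with certainty: the fourth always, and the third when the first two match (probability 1/3). The share is (1 + 1/3)/4 = 1/3.
- Expected correct guesses by position: 1/2, 2/3, 2/3 and 1. The share is (1/2 + 2/3 + 2/3 + 1)/4 = 70.8%.

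Enumerating all 70 blocks of 8 gives 20% deducible and 66.6% expected correct guesses.

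Final group sizes would not reveal a repeated A-B-B-A list. Thirteen such blocks give 13 × 2 = 26 patients per arm at 52, which is the planned split.

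**The case against.** The strongest defence is that the two sentences are a drafting remnant. The averaging sentence is in the past tense in a section written almost wholly in the future tense, and everything operational elsewhere is parallel-group. That is probably right, but it does not remove the problem. Section 3 also speaks of transference effects, and Section 4 bases its calculation on two dependent means. Both fit a within-patient design, so a reader cannot safely dismiss the sentences as a slip.

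A reader might infer that the article has published the real allocation order and that every assignment can be foreseen. The text does not support that. The sentence says what each patient completes, not how successive patients are listed. The random-number table, the two block sizes and the locked sequence all point away from a repeated four-item list. The 100% figure is conditional on the list-order reading.

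A reader might also infer from Section 2.5 that unblinded patients answer the baseline questionnaires knowing their arm, which would compromise the baseline covariate. That rests on one loose clause tied to a flow chart that is not reproduced in the text available. Section 2.2 puts assessment before random assignment, and the pain score is an entry criterion in Section 2.4, so at least one outcome scale is taken beforehand. Section 2.2 does not say that the full Pre set is collected then. What stands is a request for clarification.

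**Conclusion.** The contradiction is explicit and must be corrected: as written, Section 3 describes either a within-patient design that the trial does not have or an allocation order that is not random. This conclusion rests on the article's wording alone and needs no assumption.

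The size of any harm is not fixed by the document. If the working list is properly permuted, the defect is confined to the text. If it was built as repeated A-B-B-A, foreseeability rises from about 71% expected correct guesses (blocks of 4, size known) to 100%. It would then matter in practice, because the unblinded treating physiotherapist, who serves both groups, sees past allocations. Whether that person also takes part in recruitment is not stated. Neither a predictable list nor a compromised baseline has been shown.

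**What to change.** 1. Delete the A-B-B-A and averaging sentences from Section 3.
2. State that each patient is allocated once, to SCS or to SCS plus exercise, from a computer-generated list of randomly permuted blocks of randomly varying size. The independent researcher holds the list and releases one assignment at a time.
3. Do not rely on keeping sizes 4 and 8 secret, since the article already publishes them. Protection should come from the random order within blocks, block sizes that vary unpredictably, and release one patient at a time.
4. Have the independent researcher check the existing list. If it was built as repeated A-B-B-A, regenerate the unused part and report how many patients had already been allocated from it.
5. As a secondary clarification, reconcile Sections 2.2 and 2.5 by stating that the Pre questionnaires are completed before the allocation is revealed.

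The cost is a few sentences in Sections 2.5 and 3 and one check of the list, with no extra patients or staff. Data collection was planned from April 2024, so new wording cannot repair what has already happened. If the check finds a fixed order, or baselines taken after disclosure, the affected patients should be identified and this reported with the results.

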## 4. Sample size

The sample size will be estimated using GPower® software (Franz Faul, Universität Kiel, Kiel, Germany), version 3.1.9.2. As there are no similar studies allowing for the calculation of sample size based on reference means and standard deviations, a comparison will be made using the difference between two dependent means of 1.95 normal populations, assuming equal standard deviations of 3,2 according to the results obtained from a prior study [37]. Thus, the calculation will be based on the primary outcome of "Disability" and will consider an effect size of 0.70, a power of 0.95 for ANOVA repeated measures, and an alpha error of 0.05. A total of 40 participants (20 subjects per group) will be included in this study. Moreover, considering the probability of loss during follow-up (30%), 12 more participants considering dropout (6 participants per group) will be included, resulting in a total of 52 participants. The possibility of increasing the number of subjects will be explored in case of insufficient statistical power to reach these predefined levels. In the event of dropouts, noncompliance, or absence of results, an intention-to-treat analysis will be conducted.

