**Methods/Materials:**

A double-blind randomized clinical trial (RCT) has been designed. All participants will be randomized from a pre-set sequence. The intervention design has been elaborated from the CONSORT guidelines. This study has been registered at Clinicaltrial.gov (NCT06272539). Sample size was calculated using G Power® Sample size software (University of Düsseldorf). The calculation was based on a moderate effect size of 0.7 (partial η2 = 0.70, α = .05, power = 0.95), resulting in a total of 40 patients. Assuming a 30% dropout rate, 52 participants will be recruited in total. Two sessions per week will be scheduled for 8 weeks with a total of 16 sessions. Each work session will have a duration of 60 minutes. The exercise will be adapted according to the phases based on the results already published, limiting in each phase the degrees of flexion and extension of the spine to avoid the risk of electrode migration. Primary outcomes will be functionality, satisfaction, strength, psychosocial variables, quality of life and pain perception.

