#### 8.2.2 Analysis of the outcome measures

Following the Consolidated Standards of Reporting Trials (CONSORT) guidelines on the reporting of RCTs, a per-protocol analysis will be performed. The normality assumption will be checked with the Kolmogorov–Smirnov test and box-plot analysis, while the homogeneity of the variance will be tested through the Levene test. To analyze the acute and short-term effects of SCS and SCS combined with core and control motor exercise on PSPS T2, a two-way ANOVA for repeated measures with experimental groups (i.e., Post3weeks, Post2months, Post6months) as factors will be used, followed by Tukey corrections, to examine time, group, and interaction effects through within- and between-group comparisons (primary and secondary outcomes). The results will be presented as the mean difference (MD) and confidence interval at 95% (IC95%). Effect size (ES) will be estimated by calculating Cohen’s d coefficient. All analyses will be performed using the statistical analysis software SPSS 24 (IBM Inc., Chicago, Illinois, USA). In the case of dropouts during the study or if the statistical power is less than the established 80%, an intention-to-treat principle analysis will be performed [71]. The normality of the data will be tested by visual inspection of histograms, and the characteristics of the participants will be presented using descriptive statistical tests. To assess between-group differences in response to treatment at each post-baseline time point, the mean between-group differences and their associated 95% confidence intervals (CI) will be calculated by constructing mixed linear models using interaction terms (group vs. time). The treatment effects will be adjusted by including baseline outcome values as covariates in the model. Statistical analysis will be conducted by a researcher who is not involved in any of the phases of data collection and will receive data in coded form. Minimal clinically important differences are patient-derived scores that reflect changes in a clinical intervention that are meaningful to the patient. To do this from the delta percentage (Δ%) will calculate using the standard formula: change (%) = [(post-test score − pre-test score)/pre-test score] × 100.

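### The stated 95% power with 20 patients per group cannot be reproduced from the sample-size inputs, which conflict, and they do not support it

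*Protocol article*

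**What the plan says.** Section 4 (Sample size) of the protocol article names disability, measured by the ODI, as the basis. It takes "the difference between two dependent means of 1.95 normal populations, assuming equal standard deviations of 3,2" from a prior study. It then says the calculation "will consider an effect size of 0.70, a power of 0.95 for ANOVA repeated measures, and an alpha error of 0.05". The result is 40 patients, 20 per group, raised to 52 for dropout. The metric of the 0.70 is not named.

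The abstract describes the same calculation as resting on a "moderate effect size of 0.7 (partial η2 = 0.70, α = .05, power = 0.95), resulting in a total of 40 patients".

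Section 2.1 describes two groups allocated 1:1. Section 8.2.2 plans a two-way repeated-measures ANOVA and a mixed model adjusted for the baseline outcome. It makes an intention-to-treat analysis depend, among other things, on whether power falls short: "if the statistical power is less than the established 80" per cent.

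**The concern.** The inputs do not describe one calculation. Dependent means belong to a paired design, whereas the question is combined treatment against spinal cord stimulation alone in different patients. The number 0.70 is an unlabelled effect size in one place and a partial η2 in another, and two power targets are in force.

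Two things are at stake. First, the abstract presents the trial as having 95% power for its primary outcome. A reader would then take a null result as strong evidence against an effect of the planned size. If the real power is well below 95%, that reading is wrong. Second, the power figure drives decisions: section 4 allows more patients if the predefined levels are not reached, and section 8.2.2 ties the intention-to-treat analysis to 80%. With 0.95 in one place and 80% in the other, it is unclear which threshold governs.

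**Working it through.** **Inputs.** From section 4: difference 1.95, SD 3.2, effect size 0.70, alpha 0.05, power 0.95, N = 40 as 20 per group. From the abstract: partial η2 = 0.70. From section 8.2.2: power 80%, baseline adjustment. Assumed here because not stated: a two-sided test, and all correlations.

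**1. Attempt to reproduce N = 40 at 95% power from the stated 0.70.**
- Paired t-test, 0.70 as the standardised mean of the differences: 29 patients.
- Two-sample t-test, 0.70 as Cohen's d: 55 per arm, 110 in total.
- 0.70 as Cohen's f in repeated-measures ANOVA: about 4 to 26 in total; power at N = 40 is at least 99%.
- 0.70 as partial η2: f = √(0.70/0.30) = 1.53, or d = 2f ≈ 3.06 for two equal groups; about 4 to 8 in total.
- d = 0.70 as f = 0.70/2 = 0.35, between-group effect, assumed correlation 0.5 to 0.8, 2 to 6 measurements: 64 to 98 in total.

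None gives 40. Nearby values need other inputs. A paired test at 0.61 needs 37 patients. A group-by-time interaction test with f = 0.35, 2 measurements and correlation 0.3 gives exactly 40.

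**2. From 1.95 and 3.2 to an effect size.**
- Between groups: d = 1.95/3.2 = 0.61.
- Paired, with SD 3.2 in each condition: 1.95/(3.2·√(2(1−r))). This is 0.61 at r = 0.5. Setting it to 0.70 gives r = 1 − (0.609/0.70)²/2 ≈ 0.62, a correlation the article does not state.

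**3. Power for the between-arm comparison, 20 evaluable per arm, two-sided 0.05.** Noncentral t with noncentrality d·√(n/2). For baseline adjustment, d is replaced by d/√(1−r²), with 37 degrees of freedom.

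| Analysis | d = 0.70 | d = 0.61 |
|---|---|---|
| Unadjusted, one time point | 58% | 47% |
| Baseline-adjusted, r = 0.5 | 70% | 58% |
| Baseline-adjusted, r = 0.6 | 77% | 65% |
| Baseline-adjusted, r = 0.7 | 86% | 75% |
| Baseline-adjusted, r = 0.8 | 95% | 88% |

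For the repeated-measures group effect, the noncentrality is f²·N·m/(1+(m−1)ρ). With f = 0.35, N = 40 and ρ = 0.5, power is 75% at m = 3 visits and 81% at m = 6.

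**4. Sample size per arm, unadjusted.** For 95% power: 55 at d = 0.70 and 71 at d = 0.61. For 80%: 34 and 44.

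**5. Detectable difference with 20 evaluable per arm.** Unadjusted: d = 0.91 at 80% power and 1.17 at 95%. Baseline-adjusted with r = 0.5: about 0.91 × √(1−0.25) = 0.79 at 80%.

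**The case against.** A reader might infer that the 95% claim is simply false and that true power is 58%. The article does not support that. The 58% belongs to an unadjusted t-test at one time point, with 0.70 read as Cohen's d. Section 4 refers to repeated-measures ANOVA and section 8.2.2 adds baseline adjustment, so 58% is the low end and not the power of the planned analysis. For the same reason, missing a true effect about half the time is not a fair summary. With baseline adjustment at r = 0.5 to 0.7, the miss rate at d = 0.70 is about 14% to 30%, still well above 5%.

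Nor is 0.61 against 0.70 a strict contradiction. For dependent means both can be right at a correlation of about 0.62. What stands is that no correlation is given, and that a paired effect size does not carry over to a comparison between arms.

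It is also tempting to say that N = 40 is a one-group pre-post number split into two arms. The paired count at 0.61 (37) is close, but the interaction test in step 1 gives 40 exactly, so the origin is unknown. If an interaction f of 0.35 was intended, power at N = 40 would exceed 95% at a correlation of 0.5. That f measures the spread of interaction means, however, and is not a between-arm d of 0.70. Reading 0.70 as Cohen's f also gives over 95% power, but implies d = 1.4, which is hard to square with 1.95/3.2 or with the word moderate.

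Section 3 describes each patient completing an A, B, B, A sequence, which might seem to justify dependent means. It conflicts with the two 1:1 groups in section 2.1 and with the 20 per group in section 4.

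Finally, 52 are to be enrolled. If nobody were lost, 26 per arm would give 70% unadjusted and about 81% to 93% adjusted (r = 0.5 to 0.7) at d = 0.70. That is better, but still short of 95%.

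**Conclusion.** The point holds in this form: 95% power with 20 per group is neither reproducible from nor supported by the stated inputs. Three conflicts need no assumption: dependent means in a two-arm parallel trial, the same 0.70 labelled both moderate and partial η2, and 0.95 against 80%.

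The size of the shortfall does rest on assumptions: 0.70 is Cohen's d, the test is two-sided, and 20 per arm are evaluable. The planned types of analysis then give roughly 70% to 86%, and 95% is reached only at a baseline-outcome correlation of about 0.8. At d = 0.61 the adjusted range is 58% to 75%. Because the unsupported figure concerns the primary outcome and appears in the abstract, it should be corrected and not left for the reader to interpret.

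**What to change.** Amend the abstract and sections 4 and 8.2.2 as follows.

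- Delete the reference to dependent means and the partial η2 label.
- State one effect size, its metric and how it was derived. If 1.95 and 3.2 are kept as a between-group difference and SD, that is d = 0.61.
- State which effect is tested (group, or group by time), the number of measurements and the assumed correlation.
- Restate the power for the baseline-adjusted ODI comparison between two independent arms. Give the detectable difference at 20 evaluable per arm: about d = 0.91 at 80% power unadjusted, or about 0.79 with an assumed correlation of 0.5.
- Use the same power figure in section 4 and section 8.2.2.

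This changes wording only. The planned 52 patients, the design and the visits stay as they are. The cost is a stated power less favourable than 95%.
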